## Abstract

**Background:**

Falls are two to four times more frequent amongst older adults living in long-term care (LTC) than community-dwelling older adults and have deleterious consequences. It is hypothesised that a progressive exercise program targeting balance and strength will reduce fall rates when compared to a seated exercise program and do so cost effectively.

**Methods/design:**

This is a single blind, parallel-group, randomised controlled trial with blinded assessment of outcome and intention-to-treat analysis. LTC residents (age ≥ 65 years) will be recruited from LTC facilities in New Zealand. Participants (*n* = 528 total, with a 1:1 allocation ratio) will be randomly assigned to either a novel exercise program *(Staying UpRight)*, comprising strength and balance exercises designed specifically for LTC and acceptable to people with dementia (intervention group), or a seated exercise program (control group). The intervention and control group classes will be delivered for 1 h twice weekly over 1 year. The primary outcome is rate of falls (per 1000 person years) within the intervention period.

Secondary outcomes will be risk of falling (the proportion of fallers per group), fall rate relative to activity exposure, hospitalisation for fall-related injury, change in gait variability, volume and patterns of ambulatory activity and change in physical performance assessed at baseline and after 6 and 12 months. Cost-effectiveness will be examined using intervention and health service costs.

The trial commenced recruitment on 30 November 2018.

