## Methods

### Design and setting

An investigator and assessor-blinded, parallel-group multisite randomised controlled trial (RCT) will compare a progressive balance and strengthening exercise program (*Staying UpRight*) with a low-intensity seated exercise program (*Flex and Stretch*) provided to older people living in LTC facilities located in Auckland and Hamilton, New Zealand. The study design is outlined in Fig. 1. Reporting of results will conform to the recommendations of the Consolidated Standards of Reporting Trials (CONSORT) statement [26] and to the Standard Protocol Items: Recommendations for Interventional Trials (SPIRIT) guidelines. The SPIRIT checklist is provided as Additional file 2. Any protocol amendments will be submitted to the New Zealand (NZ) Health and Disability Ethics Committee (HDEC) for review and will be updated on the trial registry.

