### Outcome measures

#### Primary outcome

The primary outcome measure is fall rate (per 1000 person years).

Using the LTC facility’s incident report records, fall registers will be audited for the 6 months prior to study commencement (to provide baseline data) and for the 12 months of the study. Estimates of complete accuracy in fall ascertainment is impossible, as most falls are unwitnessed [4], but the possibility of increased falls being reported as programmes are implemented [27] will be avoided by using the already accepted and implemented reporting systems RiskMan™ (RiskMan International Pty Ltd., Southbank, Victoria, Australia) or VCare™ (VCare International Ltd., Burnside, Christchurch, NZ) that are standardised throughout all LTC facilities in the trial.

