### Blinding

Assessors will be blinded to group allocation for all assessments. Group assignment will only be available to the project coordinator [name], data manager [name] and the intervention coordinator [name] and will be accessed online via a password-protected site. Participants and the staff providing the intervention cannot be blinded.

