^a^Balance categories: centre of gravity control, weight transfer, postural strategies, gait training, multisensory

To test sustainability, the LTC facility staff (physiotherapist or physiotherapy assistant) will take over delivery of the classes for the second 6 months, ensuring continuity of the programme for 1 h twice weekly over the 12-month period. If the ongoing provision of classes is compromised within a facility, alternative funding streams will be sought.

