#### Intervention fidelity monitoring

To ensure fidelity of the intervention, an exercise class at each facility will be observed by a research investigator within the first 2 months of physiotherapist delivery and within the second 6 months of LTC facility delivery. A fidelity checklist which includes the number of participants, exercises completed, total time spent in standing and total class duration will be used to identify any deviations from the exercise protocol, with feedback given to the class facilitator. The research intervention coordinator will also audit all class exercise spreadsheets monthly to identify any deviations from the protocol.

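### Outcome and investigator blinding are claimed without limit, but the primary outcome, fall rate, comes from facility incident reports that nothing in the protocol blinds

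*Protocol article*

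**What the plan says.** **The claims.** The abstract (Methods/design) labels the trial single blind and a "randomised controlled trial with blinded assessment of outcome and intention-to-treat analysis". The Design and setting section opens with "An investigator and assessor-blinded, parallel-group multisite randomised controlled trial (RCT". Neither sentence excepts any outcome.

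**Who is blinded.** The Blinding section says "Assessors will be blinded to group allocation for all assessments", and then "Participants and the staff providing the intervention cannot be blinded". Access to allocation is limited: "Group assignment will only be available to the project coordinator", the data manager and the intervention coordinator.

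**Where the primary outcome comes from.** Under Primary outcome, falls are audited from each facility's incident records and fall registers. The section concedes that most falls are unwitnessed. It says that the possibility of more falls being reported once programmes start "will be avoided by using the already accepted and implemented reporting systems".

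**Who runs the classes.** Control classes are led by the facility's activities staff or a trained volunteer (Control group). A physiotherapist trained in the programme leads the intervention classes at first; facility physiotherapy staff "will take over delivery of the classes for the second 6 months" (Intervention group).

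**Class observation.** For fidelity, "an exercise class at each facility will be observed by a research investigator within the first 2 months" of physiotherapist delivery, and again in the second half of the year.

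**The concern.** Blinded outcome assessment is normally read as covering the primary outcome. Here it covers the secondary measures taken by assessors and leaves out the endpoint on which the trial is powered.

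The incidence rate ratio (IRR) from the negative binomial model uses recorded falls. If falls in the two arms are recorded with different completeness, that difference multiplies directly into the IRR. It could create an apparent benefit or hide a real one. More participants would not remove it, and comparing the arms within the same home does not remove it either. A reader who takes the primary result as blinded would not look for this. Investigator blinding is also stated without reconciling it with the roles that hold allocation or with the class observation.

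**Working it through.** **1. Does the blinding reach the primary outcome?**

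| Outcome | Source in the protocol | Blinding stated? |
|---|---|---|
| SPPB, TUG, MoCA | Trained assessors | Yes |
| Gait and ambulatory activity | Accelerometer, processed blind | Yes |
| Fall rate (primary) | Facility incident reports and fall registers | No |
| Hospitalisation for fall injury | Matched Ministry of Health data | Not addressed; depends less on facility reporting |

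No section says that the people who report falls, or whoever audits the registers, are blinded.

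**2. Can reporters be expected to know allocation?** Residents are randomised individually, stratified by facility and level of care, so both arms live under the same staff. One arm does standing balance and strength work, the other seated activity, in separate classes. Facility activities staff (or a volunteer) lead the control classes, and facility physiotherapy staff lead the intervention classes in the second 6 months. This is a strong inference; the protocol does not say it outright.

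**3. What does the safeguard cover?** The sentence containing "will be avoided by using the already accepted and implemented reporting systems" concerns a general rise in reporting once programmes are introduced. A shared, established system can limit that. It does nothing specific about reporting that differs between two residents of the same home.

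**4. Investigator blinding.** Allocation is restricted to three roles, yet a research investigator watches classes at each facility. The observer may hold one of those roles or may not; the protocol does not say.

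**5. Size, as an illustration.** Let r be the share of intervention-arm falls recorded divided by the share of control-arm falls recorded.

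Observed IRR = true IRR × r. With r = 0.90: 1.00 × 0.90 = 0.90.

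To express this as error rates, start from the plan's own sample size: control rate 2.6, intervention rate 2.6 × 0.75 = 1.95, two-sided 0.05, power 90%, one year each, negative binomial dispersion k.

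n per arm = (1.960 + 1.282)² × (1/2.6 + 1/1.95 + 2k) / (ln 0.75)²

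- k = 0 gives 114.
- n = 264 requires k = 0.59: 10.507 × (0.3846 + 0.5128 + 1.1819) / 0.08276 = 264.

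The article does not give k, which is usual at this length, and the 264 is not disputed. Taking k = 0.59 as an assumption, with 264 per arm:

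SE = √[(1/2.6 + 1/(2.6 × observed IRR) + 2k) / 264]

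Example, no true effect, r = 0.90: SE = √[(0.3846 + 0.4274 + 1.1819) / 264] = 0.0869; ln 0.90 / SE = −0.1054 / 0.0869 = −1.21; chance of a significant result favouring the intervention = Φ(−1.96 + 1.21) ≈ 0.23.

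| True IRR | r | Observed IRR | Chance of a significant result (two-sided test) |
|---|---|---|---|
| 1.00 | 1.00 | 1.00 | 5% |
| 1.00 | 0.95 | 0.95 | 9% |
| 1.00 | 0.90 | 0.90 | 23% |
| 1.00 | 0.85 | 0.85 | 46% |
| 1.00 | 0.80 | 0.80 | 72% |
| 0.75 | 1.00 | 0.75 | 90% |
| 0.75 | 1.05 | 0.7875 | 77% |
| 0.75 | 1.10 | 0.825 | 59% |

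The documents give no value of r. The table shows sensitivity only.

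**6. How much can the injury analyses check?** At the 5% yearly fracture figure in the Background, 0.05 × 264 ≈ 13 residents per arm would have a fracture. Treating these as 13.2 events per arm, the SE of the log rate ratio is √(1/13.2 + 1/13.2) = 0.39, so 95% limits lie a factor of exp(1.96 × 0.39) ≈ 2.1 either side. That cannot detect a 10% reporting difference.

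**The case against.** The protocol is open about much of this. It calls the trial single blind, says that participants and delivery staff are not blinded, and lists who holds allocation. Stratification by facility means that one reporting system serves both arms, which limits differences between homes. These points stand, but none of them says that fall ascertainment is unblinded.

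Several stronger readings are tempting and are not supported:

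- *The protocol claims to have prevented differential reporting.* It does not. The avoidance claim is about a general rise in reporting.
- *Because most falls are unwitnessed, reporting is at staff discretion.* Unwitnessed falls limit completeness; nothing says that staff may choose whether to report.
- *The people leading classes are the people filing reports.* The protocol does not say who files them. A volunteer may lead control classes, and facility staff lead intervention classes only in the second 6 months.
- *Class observation disproves investigator blinding.* The observer's role is not identified and three roles are already excepted. The statements need reconciling; a breach affecting outcome data is not shown.
- *Reporting bias could supply the whole target effect.* Taking a true IRR of 0.83 to 0.75 with r = 0.90 leaves 17 of the 25 percentage points as real effect and adds about 8 by bias, and the 0.90 has no source in the documents.
- *No less reporter-dependent analysis is planned.* Hospitalised fall injury from matched national data is already a secondary outcome, and fall-injury models are already in the Statistical analysis section.

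Who audits the registers, and whether masked, is detail that an article commonly leaves to the full protocol. Its absence here is not a fault in itself.

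**Conclusion.** The point holds as a mismatch between claim and design. Outcome and investigator blinding are stated without exception, while the stated blinding covers only the assessors' measurements and the primary outcome comes from facility incident reports made by people who can be expected to know allocation. A separate analysis plan would not cure this, because the broad statements are made affirmatively in this document.

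The consequence is a limit on interpretation: the primary IRR should be read as based on unblinded reporting. A reader might infer that the result will be biased, or biased in favour of the intervention. The documents support neither. Size and direction are unknown, and the figures above rest on an assumed r, an assumed k of 0.59 and one full year of follow-up per participant. They show only that differences of 5% to 20% in completeness would matter at this sample size. Individual randomisation is a reasoned choice under Contamination and need not change.

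**What to change.** - In the abstract and in Design and setting, limit the blinding claim to the assessor-measured outcomes (SPPB, TUG, MoCA, accelerometry), and state that fall reporting by facilities is unblinded.
- Have the fall registers audited by an existing team member without access to allocation. If the full protocol already provides for this, say so.
- Reconcile investigator blinding with the list of roles that hold allocation and with the fidelity observation: state which investigators are blinded and whether the class observer is one of them.
- Under Primary outcome, say that a general rise in reporting may be reduced by the existing systems, not that it is avoided, and acknowledge that they do not address reporting that differs by arm.
- Name the planned matched-hospitalisation outcome and the fall-injury models as supportive checks that depend less on reporters, and note their low precision.

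The cost is wording and an assignment within the existing team; no new data or analyses are needed. The downside is a weaker blinding statement.

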**Discussion:**

This study evaluates the efficacy and cost-effectiveness of a progressive strength and balance exercise program for aged care residents to reduce falls. The outcomes will aid development of evidenced-based exercise programmes for this vulnerable population.

**Trial registration:**

Australian New Zealand Clinical Trials Registry ACTRN12618001827224. Registered on 9 November 2018. Universal trial number U1111-1217-7148.

## Background

Worldwide, falls account for 0.85–1.5% of total annual healthcare expenditures (0.2% of global gross domestic product), with each fall costing up to US$26,000 [1]. Falls are two to four times more frequent in long-term care (LTC) dwellers than in community dwellers [2, 3]. More than 60% of LTC residents fall annually, and fall rates are highest in low dependency care [4, 5], with 5% of LTC residents sustaining a fracture yearly [6].

The mechanisms involved in falls are complex and differ depending on the environmental context and intrinsic risk factors [7]. Video observations of falls in older adults under LTC show two main causes: incorrect weight-shifting during transfers or when turning, and tripping due to inadequate foot clearance [8]. One third of falls in LTC dwellers involve head impact [9], and these falls account for 19% of all traumatic brain injury hospitalisations in older adults [10]. Falls in LTC residents involving head impact most often occur when falling forward whilst walking, with the outstretched hand no longer an effective protective response against impact [9].

Risk factors for falls in LTC occupants are multifactorial. Balance, muscle strength, gait and cognitive impairments all significantly increase the risk of falls [11–13]. Cognitive impairment compromises ‘top down’ control of gait and balance, which is required for navigating the environment [14, 15]. People with dementia are eight times more likely to fall than those without dementia [16], and falls account for 26% of hospital admissions in those with dementia [17]. Increased fall risk in LTC dwellers is associated with a history of falls, walking aid use, moderate disability, wandering, Parkinson’s disease, dizziness, use of sedatives, antipsychotics or antidepressants and higher number of medications used [18].

Management of fall risk reflects this complex presentation, but with mixed outcomes. Pooled results from multifactorial programmes targeting LTC residents’ individual risk profiles show no significant reduction in fall rates [19]. Similarly, pooled results indicate the effect of exercise as a single intervention on the rate of falls in LTC dwellers is uncertain; heterogeneity, protocol weaknesses and small sample sizes limit the conclusions (rate ratio [RaR] 0.93, 95% confidence interval [CI] 0.72–1.20; 2002 participants, 10 studies). Notably, few exercise programmes reviewed were longer than 14 weeks, and the degree of inclusion of people with dementia was not consistently reported. Given that more than 60% of LTC residents have dementia [20], their inclusion in fall prevention programmes is critical. A review of exercise for falls in people with dementia showed positive results [21] (RaR 0.68, 95% CI 0.51–0.91; 781 participants, 7 studies), although few trials were set in LTC facilities.

An exercise program developed by this group, *Staying UpRight*, was successfully piloted in care homes in 2008 [22]. The *Staying UpRight* program is based on an understanding of the physiological systems of balance and includes exercises to challenge these systems, i.e. muscle strength, visual integration, vestibular adaptation, balance strategy retraining and sensory integration. It adheres to principles of rehabilitation, namely appropriate tailoring of dose, intensity and progression by the therapist. Adherence to these principles makes *Staying UpRight* unusual in the LTC setting, where activities are usually undertaken seated, are not tailored to individual ability and are not progressed. The pilot reported improvements in physical function (nonsignificant), with no adverse events and, importantly, attendance of 60% at classes. The program was also acceptable to participants and staff. Based on the success of the pilot, the current trial is powered to test the effect of the *Staying UpRight* program on reducing the rate of falls over a 12-month period.

A second, novel feature of this study is reporting of activity-adjusted fall risk, using wearable accelerometers to measure continuous activity. Falls may reduce as people become less active (reduced exposure to risk), not because of improvement in motor function. An exercise program that improves mobility may therefore increase the number of falls. This potential trade-off has not been tested to date in LTC settings [23–25]. Activity patterns may also provide more insight into the dynamic nature of fall risk [7] and will be explored alongside falls in the context of ongoing cognitive decline.

This study tests the primary hypothesis that the *Staying UpRight* exercise program, when compared to seated exercises, will be effective in reducing falls in LTC facilities. Secondary hypotheses are that the *Staying UpRight* program will:
Reduce falls, fall-related injuries and the risk of fallingIncrease the volume and change the pattern of ambulatory activityBe cost-effective when compared to seated exercise.

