#### Secondary outcomes

Secondary outcome measures are:
*Risk of falling*, expressed as proportion of fallers per group, i.e. those who sustained at least one fall during follow-up.*Rates of hospitalisation for fall-related injury* (fracture, intracranial or extracranial haemorrhage), expressed as number of fall hospitalisations per 1000 person years of follow-up. Hospitalisation data will be collected from National Health Index (NHI) matched Ministry of Health data over 12 months.*Fall rate relative to activity exposure,* expressed as number of falls per 100,000 steps. Participants will wear a tri-axial accelerometer (Axivity AX3; Axivity, York, UK), secured on the lower back at the fifth lumbar vertebrae (L5) using a hydrogel adhesive (PALStickies, PAL Technologies, Glasgow, UK), covered with an adhesive dressing (OPSITE Flexifix™ and Hypafix™, Smith+Nephew Ltd., Watford, UK). The accelerometer is programmed to sample at a frequency of 100 Hz (range ± 8 g).*Gait volume, pattern and variability of ambulatory activity*, measured using accelerometry as described above. Algorithms are valid for gait spatio-temporal features for macro gait, i.e. volume (total steps, time spent walking, bout number), pattern of activity (bout length and bout distribution), variability of ambulatory bouts and microgait, i.e. pace, rhythm, variability, asymmetry and postural control domains of gait [28–30].*Physical performance*, measured using the Short Physical Performance Battery (SPPB) [31] and the Timed Up and Go (TUG) test [32, 33]. The SPPB comprises ability to stand for 10 s (with feet side by side, semi-tandem and tandem stance), timed chair stand (five times chair rise) and gait speed (measured over 3 m). The maximum score is 12, with higher scores indicating better function. The TUG test requires the participant to rise from a chair, walk 3 m quickly but safely to a mark on the floor, turn, walk back and sit down. A lower time indicates better function.*Cost-effectiveness* of *Staying UpRight* versus seated exercise will be estimated as both an additional cost per fall prevented and per fall requiring hospitalisation.

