### Assessments

Demographic and health information (health conditions, medications, independence in activities of daily living) will be collected using a standardised Minimum Data Set (MDS 2.0; interRAI Corporation 1999) at baseline prior to randomisation. The interRAI™ (International Resident Assessment Instrument) Long-Term Care Facilities (LTCF) assessment is a standardised comprehensive observational assessment, completed on admission and 6-monthly thereafter by nursing staff for all residents in LTC.

Cognitive function will be measured at baseline and at 6 and 12 months using the Montreal Cognitive Assessment (MoCA) [34]. The MoCA comprises 16 items to assess multiple cognitive domains. A score of ≤ 10/30 is considered severe cognitive impairment, 11–18 moderate impairment, 19–23 mild and > 23/30 normal cognitive function [35].

Ambulatory activity over 7 days will be collected using the tri-axial accelerometer and data uploaded to an encrypted, secure platform (eScience Central online platform, Newcastle University, UK) [36] for storage and blinded processing.

Outcome measures will be completed at baseline and at 6 and 12 months (Fig. 2). Assessors will be trained in all aspects of participant assessment, activity monitoring and digital data management to ensure the assessments are standardised. Assessors will watch a standard assessment and each will rate the responses. Responses will be compared and discussed.

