### Statistical analysis

The primary analysis will be conducted on an intention-to-treat basis using data from all randomised participants, although a ‘per protocol’ analysis of the primary outcome will also be reported.

Total number of falls, number of fallers, people sustaining a fall-related fracture or brain injury; fall rate (falls per 1000 person years); multiple fallers and number in each analysis will be reported. Prior fall-incidence rates will be calculated as number of falls/resident/year using the audited 6 months prior to enrolment.

Negative binomial regression models will be fitted to determine the incidence rate ratio (IRR) for differences in fall rates between groups both for overall follow-up time as the primary endpoint and secondarily as activity-adjusted rates. Similar negative binomial models will be built for fall injury rates; fractures and head injuries both combined and separately. Logistic regression models for fallen during follow-up or not fallen and for having fallen multiple times during follow-up or not fallen will be compared between the intervention and control groups.

All models will control for prior fall rate, level of dependency and cognition (MoCA), as these are confounding factors. Baseline data will be compared between the two groups, with any strongly imbalanced factors further adjusted for in the analysis.

Per protocol analyses will be performed including those with higher attendance, and pre-planned subgroup analyses will include those with moderate and high levels of cognitive impairment.

Fall rate relative to activity exposure will be calculated and compared between groups. Within-group change will be examined using repeated measures. Generalised linear mixed-effects regression models will be used for volume, pattern and variability of ambulatory activity and cognition.

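### Baseline SPPB, a measure of three named fall risk factors, should be a pre-specified covariate in the primary fall-rate model, not one admitted only by chance imbalance

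*Protocol article*

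**What the plan says.** All references are to the protocol article.

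- **Background** lists impairments that raise fall risk: "Balance, muscle strength, gait and cognitive impairments all significantly increase the risk of falls".
- **Secondary outcomes** describes the physical performance test: "The SPPB comprises ability to stand for 10 s (with feet side by side, semi-tandem and tandem stance), timed chair stand", followed by gait speed. It thus covers balance, leg strength and gait.
- **Assessments** gives the timing: "Outcome measures will be completed at baseline and at 6 and 12 months". **Randomisation** places allocation after the baseline assessment, so baseline SPPB cannot be affected by treatment.
- **Statistical analysis** defines the primary model: "Negative binomial regression models will be fitted to determine the incidence rate ratio (IRR) for differences in fall rates between groups". It fixes the covariates: "All models will control for prior fall rate, level of dependency and cognition (MoCA), as these are confounding factors". It gives one further route into the model: "Baseline data will be compared between the two groups, with any strongly imbalanced factors further adjusted for in the analysis".

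Of the four impairments in the Background sentence, only cognition is adjusted for directly. SPPB is not on the fixed list and can enter only through the imbalance rule.

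**The concern.** In a randomised trial, baseline factors differ between arms only by chance. The reason to adjust for one is that it predicts the outcome, because that removes explained variation from the dispersion term and narrows the interval for the rate ratio. Observed imbalance is a poor guide to this: a strong predictor that happens to be balanced stays out, and a weak one that happens to be imbalanced goes in.

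The imbalance rule also leaves the final form of the primary model to be settled after the baseline data have been seen. For a measure so close to what the intervention trains, it is better to settle this in advance.

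Two things are at stake: some precision in the primary rate ratio, from data the trial collects anyway, and a primary model fixed beforehand.

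**Working it through.** **Inputs.** From Sample size estimation: control rate 2.6 falls per resident-year, 25% reduction (so 1.95), 264 per arm, two-sided 5%, power 90%. Assumed: one year of follow-up each, a negative binomial dispersion k (none is stated), and a share R of the residual dispersion removed by SPPB (no association is given).

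**Step 1: reproduce the plan's figure.** For a log rate ratio,

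n per arm = (z₀.₉₇₅ + z₀.₉₀)² × (1/2.6 + 1/1.95 + 2k) / (ln 0.75)²

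Here (z₀.₉₇₅ + z₀.₉₀)² = 10.507, 1/2.6 + 1/1.95 = 0.897 and (ln 0.75)² = 0.0828.

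- Poisson (k = 0): 10.507 × 0.897 / 0.0828 ≈ 114 per arm, not 264.
- Solving for n = 264: 0.897 + 2k = 264 × 0.0828 / 10.507 = 2.079, so k = 0.59.

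The 264 is therefore consistent with k of about 0.59, but it cannot be confirmed from the stated inputs. If the 35% drop-out had already been built into the 264, the implied k would be about 0.23.

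**Step 2: how much of the variance a covariate can reach.** At k = 0.59, dispersion makes up 1.182 / 2.079 = 57% of the variance of the log rate ratio. The other 43% is Poisson variation, which adjustment does not remove.

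**Step 3: add SPPB.** Replace k by k(1 − R) and compute power at 264 per arm as Φ(|ln 0.75| / √[(0.897 + 2k(1 − R)) / 264] − 1.96). This treats k as the dispersion left after the planned covariates.

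| k | R | Variance ratio | Power | n per arm for 90% |
|---|---|---|---|---|
| 0.59 | 0 | 1 | 90.0% | 264 |
| 0.59 | 5% | 0.972 | 90.8% | 257 |
| 0.59 | 10% | 0.943 | 91.6% | 249 |
| 0.59 | 20% | 0.886 | 93.1% | 234 |
| 1.0 | 0 | 1 | 78.4% | 368 |
| 1.0 | 5% | 0.965 | 79.8% | 356 |
| 1.0 | 10% | 0.931 | 81.2% | 343 |
| 1.0 | 20% | 0.862 | 84.1% | 318 |

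At k = 0.59 the gain for R of 5% to 20% is 0.8 to 3.1 power points, or 7 to 30 fewer residents per arm for the same power.

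**Step 4: check with prior falls already in the model.** In 400 simulated trials per setting (528 residents, total dispersion about 0.59, a prior six-month fall count generated from the same underlying risk), adjusting for prior falls alone cut the variance of the treatment effect by about 18%. Adding SPPB cut it further by these amounts:

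| SPPB share of total log-rate variance | Further variance cut |
|---|---|
| 0 | none |
| 5% | about 1% |
| 10% | about 2% |
| 20% | about 5% |
| 30% | about 8% |

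Here 0.59 is the dispersion before any adjustment, so the planned covariate has already raised power. At the 20% share the mean standard error falls from 0.0770 to 0.0750. Power is then Φ(0.2877/0.0770 − 1.96) = 96.2% against Φ(0.2877/0.0750 − 1.96) = 97.0%, a gain of under one point. The 1 to 3 points in Step 3 therefore require 0.59 to be what remains after the planned covariates.

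The simulation entered SPPB as a log-linear normal covariate and left out dependency and MoCA. It indicates the order of magnitude and is not a forecast for a categorical or spline term.

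**The case against.** **The plan breaks no rule.** It pre-specifies three covariates, including prior fall rate, and leaving out a fourth neither biases the randomised comparison nor inflates the type I error. This stands in full. A reader might infer that the primary result would be biased or confounded without SPPB; nothing in the documents supports that. The point concerns efficiency and pre-specification.

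**The gain may be nil.** Poor balance, strength and gait should already show in prior falls and level of dependency. This also stands. A reader might infer that precision is certainly lost, or that a variance cut near 16% is to be expected. A cut of that size needs a rate ratio of about 1.5 per standard deviation of SPPB in a model without the planned covariates, so it is an upper bound. The documents give no figure for the association after adjustment.

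**The Background names other risk factors too**, among them walking aid use, Parkinson's disease, sedatives and number of medications. That is so, but SPPB is a single composite covering three of the four impairments in the leading sentence, so its claim is stronger than that of any one other item.

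**SPPB may be unobtainable in some residents.** Only bed-bound residents are excluded for immobility, and dementia-level care is included. In a complete-case fit, missing scores would remove residents and could cancel a small gain. This is a fair warning about how SPPB is entered, and a separate category for inability to perform the test meets it.

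**The relation may not be monotone.** The Background puts the highest fall rates in low dependency care. A single linear term could therefore gain little, which is a reason for categories or a spline.

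**Conclusion.** The point holds as a low-cost improvement. The protocol article collects, before randomisation, a measure of three impairments that it names as significant fall risk factors, and then leaves its use in the primary model to chance imbalance. The intention-to-treat rate ratio stays unbiased. What is probably forgone is some precision, and the primary model depends on the data where it need not.

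The expected gain is about 1 to 3 power points. That assumes one year of follow-up each, a dispersion of about 0.59 remaining after the planned covariates, and SPPB removing 5% to 20% of it. It is smaller if 0.59 is the dispersion before adjustment, and close to zero if SPPB adds nothing beyond prior falls, dependency and MoCA. At an assumed dispersion of 1.0 the same range of R gives 1.4 to 5.7 points (78.4% to 79.8% and 84.1%).

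**What to change.** In Statistical analysis, name baseline SPPB as a pre-specified covariate in the primary negative binomial fall-rate model, whatever the observed balance. Enter it in categories or as a spline. Code inability to perform the test as its own category, so that no randomised resident drops out of the model for that reason. Keep imbalance-triggered adjustment as a sensitivity analysis only. Make the change before allocation is unmasked for the analysis.

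The cost is one or two sentences of analysis text and a few extra parameters in a model for 528 residents. No new data, visits or participants are needed.
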